## Methods: participants, interventions, and outcomes

### Study setting {9}

The study will be conducted in Suba South Sub-County, Homa Bay County, Kenya. According to the most recent national census in 2019, Suba South Sub-County has a land area of 634.1 km^2^ and a population of 122,383 in 27,635 households [12]. Most of the population belongs to the Luo ethnic group, except some residents belonging to Suba ethnic group. The primary occupations of people are fishing in the lake and farming. Most of the household possesses more than two house structures. The main dwelling units are typically made of mud walls with metal sheet roofs, although units with walls made of iron sheets, concrete, or stones are also common [12].

In general, the Lake Victoria region has two rainy periods annually: the long rainy season from March to June and the short rainy season from August to October, though irregular patterns have been observed in the last few years. Malaria incidence peaks 1 to 2 months after the rainy season. The major vectors are *Anopheles gambiae* s.s., *An. arabiensis*, and *An. funestus* [13].

Suba South Sub-County has 30 public health facilities (2 county hospitals, 8 health centers, and 20 dispensaries). The area is divided into health units, each of which consists of 50 to 100 households. The health status of residents in each health unit is monitored by a community health volunteer (CHV). Under a Homa Bay County Government mandate, CHVs are to test suspected malaria cases with an RDT and administer the ACT to treat confirmed positive cases. LLINs are distributed for free by the government periodically, and the next distribution is planned for early 2021.

### Eligibility criteria {10}

In this study, we plan to have a baseline household survey with a blood sampling of the household members, a financial incentive intervention, and a follow-up household survey with a blood sampling of the household members.

The inclusion criteria for the baseline survey are (1) the households of at least one permanent resident aged 18 years or older at the time of the census in the coastal communities in Suba South Sub-County, where the census was conducted and (2) informed consent provided by at least one adult in the household. The inclusion criteria for the baseline blood sampling are (1) members residing in the households that participate in the baseline survey and (2) informed consent provided by themselves or the parent or legal guardian. The exclusion criterion is having severe chronic illnesses. The inclusion criteria for the financial incentive intervention are (1) members of the households that participate in the baseline survey and agree to participate in the follow-up survey and (2) informed consent provided by at least an adult member. The inclusion criteria for the follow-up survey are (1) households in which at least an adult member provides informed consent both in the baseline survey and the financial incentive intervention and (2) informed consent provided by at least one adult in the household. The inclusion criteria for the follow-up blood sampling are (1) members residing in the households that participated in the baseline survey and (2) informed consent provided by themselves or the parent or legal guardian. The exclusion criterion is having severe chronic illnesses.

Table 1 summarizes these criteria.

**Table 1 Tab1:** Inclusion and exclusion criteria for the intervention and prospective cohort survey

Inclusion criteria	Exclusion criteria
**Baseline (survey)**	
At least one permanent resident aged 18 years or older in the household	
Informed consent provided by at least one adult in the household	
**Baseline (blood sampling)**	
Members residing in the households participated in the baseline survey	Severe chronic illnesses
Informed consent provided by the parent or guardian before each survey	
**Financial incentive intervention**	
Household members residing in the households participated in the baseline survey	
Informed consent provided by at least one adult in the household	
**Follow-up (survey)**	
Households participated in the baseline survey	
Informed consent provided by at least one adult in the household	
**Follow-up (blood sampling)**	
Household members residing in the households participated in the baseline survey	Severe chronic illnesses
Informed consent provided by the parent or guardian before each survey	

### Who will take informed consent? {26a}

Written informed consent will be obtained by study team members fluent in the local languages (Luo), Swahili, and English and who fully understand the study protocol. After eligibility is confirmed, study team members will present to the potential participants a document containing all relevant information about the study in Luo and English. If the participant cannot read, study information will be conveyed verbally by a study team. The potential participants will have opportunities to ask any questions. Agreement to participate is sought only after the participant indicates an appropriate understanding of the study.

### Additional consent provisions for collection and use of participant data and biological specimens {26b}

The study information document for the financial incentive intervention contains the study overview. In addition, the documents for baseline and follow-up surveys and blood samplings contain details on collecting, storing, and using personal data and biological specimens during the study.

## Interventions

### Explanation for the choice of comparators {6b}

In Kenya, LLIN is the most widely used malaria preventive measure. The Division of National Malaria Programme coordinates free LLIN distribution, and the county governments deliver LLINs to residents in all endemic counties every 3 years. The primary purpose of this trial is to evaluate two forms of financial incentive intervention combined with malaria education and their spillover effects. Thus, all the target households will have no restrictions on their behaviors and actions, such as the use of malaria prevention measures and treatment-seeking behaviors. Therefore, although households in the control arm and the untreated households in the intervention arms will have neither incentive nor malaria education, they will be expected to take the current best practices. As for the planning stage, there is no plan for new LLIN distribution during the study period.

### Intervention description {11a}

After the baseline survey and blood sampling, the survey team will have site visits to the households in all the target 92 clusters for the intervention. In the control clusters, the survey team will explain the follow-up survey that will be held in 6 months, confirm their continuous participation in the study, and conduct a short interview in the local language, Luo. In the intervention clusters, in addition to the explanation of the follow-up survey and the confirmation of the participation, the survey team will inform that the intervention would be piloted to the household, that the eligibility for the intervention would depend on a number of a scratch card to be drawn by a household representative, that an even number will make the household eligible for the intervention, and that an odd number will make the household ineligible. The survey team will explain the reward scheme of the CCT in the CCT clusters and that of the LIS in the LIS clusters, respectively, and the timing of the follow-up survey (in 6 months). If the household representative, typically the household head or spouse, understands the incentive scheme correctly, he/she will be asked to draw a card from an envelope containing ten cards. If he/she does not understand, the survey team will explain the rule again before he/she draws a card. If an even number is drawn, he/she will be informed that the household receives the treatment, i.e., its members become eligible for the reward scheme and asked to watch the malaria education material on a tablet device that the survey team will bring, and then proceed to a short interview. Otherwise, he/she will be informed that the household does not receive the treatment, and the survey team will conduct a short interview only. Appendix has the instruction script for enumerators in the intervention to be used.

### Criteria for discontinuing or modifying allocated interventions {11b}

Since the financial incentive intervention is a promise to the eligible household members that the project will give rewards conditioning on their malaria RDT negative status in the follow-up blood sampling conducted in 6 months, it will not cause any health risks to the participants. Thus, the intervention will be discontinued only when the participants request their disinvolvement from the study or the participants migrate out of the coastal communities of Suba South Sub-County, where the census was conducted. We do not allow any crossover from the control arm to the intervention arm during the follow-up period. Those who migrate between the arms or emigrate from the study areas will be dropped from the study follow-up.

### Strategies to improve adherence to interventions {11c}

Adherence to the intervention in this study is defined as being members of eligible households of the financial incentive intervention during the period between the intervention and the follow-up. Adherence is monitored by the study team at the blood sampling visit at the follow-up to collect the blood samples.

### Relevant concomitant care permitted or prohibited during the trial {11d}

There is no specific concomitant care prohibited during the trial. All participants in all the arms will continue to receive and use free LLIN and have access to standard medical care, including malaria testing by RDT and treatment with ACT provided by the private and public service sectors.

### Provisions for post-trial care {30}

All participants will be under the normal healthcare system in the study setting. No perceived health risks for the intended population are expected with the intervention. Our plan of continuous cross-sectional malaria surveillance after the study period allows us to monitor further parasite transmission in the population.

### Outcomes {12}

The primary outcome of the study is malaria prevalence by PCR in children (0 to 15 years old) 6 months after the financial incentive intervention. The secondary outcomes are (i) malaria prevalence by PCR all the age groups for 6 months post-intervention; (ii) microscopic malaria prevalence in children and all the age groups at 6 months post-intervention; (iii) the proportion of the participants who sleep under the bed net at 6 months post-intervention; and (iv) malaria knowledge among the adults, which will be tested using a malaria quiz based on the malaria education contents.

### Participant timeline {13}

The study flowchart is presented in Fig. 2, and the study timeline is presented in Table 2.

**Fig. 2 Fig2:**
[figure not shown]
The study flowchart and sampling timeline

**Table 2 Tab2:**
[figure not shown]
Study timeline

### Sample size {14}

The malaria RDT positivity among residents in our target area is approximately 30%, based on an independent survey conducted at the same time in our study area. Our census survey suggested an approximate average household size of 5. We aim to detect the expected effect of 30% RDT positivity reduction (to 21%) relative to control both in the direct and spillover effects, with a power of 0.8, a two-sided type-I error of 5%, a cluster size of 20 households, and an intra-cluster correlation coefficient of 0.05. We rely on the optimal saturation [11] and find the required number of clusters is 28 for the control arm and 32 for the treatment arm, where ten households in a treatment cluster end up receiving the treatment, and the remaining ten households are left untreated. We have two intervention arms, each of which to compare to the control arm. Therefore, our total intervention sample consists of 9200 individual subjects from 1840 households grouped into 92 clusters.

### Recruitment {15}

#### Community sensitization

We first sought approval from the Homa Bay County Government Ministry of Health and, based on their advice, hosted meetings with CHVs, village chiefs, and Public Health Officers in Suba South Sub-County, and other key stakeholders from the county to explain the purpose, scope, objectives, methods, timeline, and potential significance of our study. CHVs and village leaders were asked to disseminate study information to and answer questions from community members. Feedback from CHVs and village leaders was sought, and regular meetings were held among CHVs, village leaders, and the study team to devise and refine approaches to engage communities. Finally, broad-level community consent to participate in this experimental intervention was sought through CHVs and village chiefs.

#### Community census

After community sensitization and affirmation of agreement to participate provided by village chiefs, a census is conducted by CHVs and experienced local research assistants to enumerate and record demographic information from all households in the health units that are receptive to our study. The following information is collected from each household: (1) the number of residents; (2) the age, gender, and occupation of each resident; (3) the number, type, size, and functions of house structures; (4) current LLIN ownership and usage; and (5) GPS coordinates of the household. Written informed consent to participate in this intervention project will be sought from the head of each household during census house visits.

## Assignment of interventions: allocation

### Sequence generation {16a}

Random numbers that follow uniform distribution between 0 and 1 are generated using R, the statistical software, and assigned to each cluster of 20 compounds. The seed of the quasi-random number is set to a 8-digit integer of “*yyyymmdd*” format, where “*yyyy*” is the year, “*mm*” is the month, and “*dd*” is the day of the date of conducting randomization. Therefore, the seed would be 20,210,930 if the randomization was to be done on the 30th of September, 2021. For this procedure, R built-in functions set.seed() and runif() are to be used.

### Concealment mechanism {16b}

Each cluster is assigned the computer-generated quasi-random number generated in the way described above after the stratification of two baseline indicators: the number of children aged 0 to 15 and their malaria prevalence. The stratification creates four (2 × 2) strata. Then, clusters are arranged in ascending order of their assigned random numbers by stratum. In each stratum, seven clusters with the smallest random numbers are assigned to the control arm, 8 clusters with the next smallest numbers are assigned to the CCT arm, and 8 clusters with the largest random numbers are assigned to the LIS arm. There will be 28 control, 32 CCT, and 32 LIS clusters in total.

### Implementation {16c}

For the arm assignment to clusters, the allocation sequence and random assignment are generated by a volunteer who has no knowledge about the study. Local study assistants will perform participant enrollment.

## Assignment of interventions: blinding

### Who will be blinded {17a}

Firstly, the arm assignment to clusters will not be disclosed to the trial participants. Thus, the trial participants do not know what arm options exist other than the arm assigned to the cluster to which the household belongs. However, there is a possibility that the information on the arm assignments can be known by the trial participants through social interactions across clusters. We try to collect such information flow across clusters in surveys.

Secondly, the treatment assignment within the intervention arms (CCT and LIS arms) will be done at the household level by using a randomly drawn card by the household representatives themselves. Therefore, the household representatives in the intervention arms know if their household belongs to one of the intervention arms and their treatment status.

Thirdly, the study team members who participate in field activities cannot be blinded since each covers several clusters with different arm assignments and implements the household-level randomization for the treatment in the intervention arms. However, laboratory- and office-based personnel (e.g., microscopists and laboratory technicians) will be blinded to the identity and intervention status of the trial participants since all biological specimens will be identified by a unique numeric study identifier, and personal information will be removed before analyses.

### Procedure for unblinding if needed {17b}

This is a socioeconomic intervention providing financial incentives and malaria education, and hence, no physical damages are expected to occur to the participants with the treatment. Therefore, there is no circumstance that they need to be unblinded.

## Data collection and management

### Plans for assessment and collection of outcomes {18a}

#### Baseline and follow-up surveys

Malaria prevalence will be estimated using cross-sectional malariometric surveys. These surveys will be conducted at baseline (before the intervention) and 6 months post-intervention. Malaria status will be determined using three methods: RDT, microscopy, and PCR. First, a finger prick blood sample will be collected for on-site diagnosis by Paracheck-Pf® RDT (Orchid Biomedical Systems, India). Survey participants with positive test results will receive a treatment course of artemether-lumefantrine with dosing instructions as per the guidelines from the Ministry of Health in Kenya. Blood smears will be prepared on-site and transported to the main laboratory in Homa Bay, where thin smears are fixed with methanol. All smears are stained with 3% Giemsa solution for 30 min and then examined by experienced microscopists. Two blood samples (70 µl each) will be collected with a 75-mm EDTA-coated micro-hematocrit capillary tube (Marienfeld, Lauda-Königshofen, Germany) and spotted on Whatman ET31 Chr filter paper (Whatman International. Maidstone, UK). The blood spots will be allowed to dry at ambient temperature and stored in individual zipped plastic bags at − 20℃. The dried blood spots (DBS) will be used for DNA extraction and determination of malaria status by PCR [14].

Malaria incidence will be assessed at the baseline and follow-up after 6 months post-intervention. CHVs will visit the households of the participants. A structured questionnaire created using the CSPro application and loaded on an Android-based tablet computer will be used to collect any history of fever, malaria episode, or visit to the local health facilities in the previous 3 months [15].

Training sessions will be held for CHVs to familiarize themselves with the questionnaire’s content and the CSPro application’s use to record the responses. Built-in validation and completion checks will ensure data quality and completeness, respectively. To avoid duplication, all microscope slides, filter papers, and sample tubes will be pre-labeled with auto-generated serial numbers. CHVs and certified medical laboratory staff will be prompted by the CSPro application before blood sampling to confirm the identity and serial number of the cohort participant. The completeness of blood sampling will be confirmed twice after the sampling step in the field and at the sample storage step in the laboratory.

#### Acceptability of the financial incentive schemes

Focus group discussions (FGDs), a structured questionnaire, and in-depth interviews will be used to assess the acceptance of the financial incentive schemes. At the end of the 6-month follow-up, a representative of all the target households will be subjected to the structured questionnaire, and a part of them will be invited to in-depth interviews based on their responses to the questionnaires.

### Plans to promote participant retention and complete follow-up {18b}

In this survey, CHVs will make an appointment with participants and confirm their available date and time at least a week before each household visit. The participants will receive a small remuneration (i.e., sugar, rice, beans, cooking oil, or soap) after the follow-up survey. CHVs will be instructed to relay to the research team any issue raised by cohort participants, and discussions will be held to resolve issues that cannot be immediately addressed. The research team will periodically accompany the CHVs in their home visits to reinforce to cohort participants the importance of the study.

### Data management {19}

Study data will be collected on Android-based tablet computers using the CSPro application to promote data quality and security. Data validation, such as range checks and completeness checks, will be enabled in all survey instruments. For the baseline and follow-up surveys, data will be uploaded to the CSPro server at the conclusion of each survey day. After the data manager confirms the data quality on the server, data stored locally on the tablet computers will be deleted before the next survey to avoid potential overwriting of existing data. Survey data will be uploaded to the CSpro server at least once a week for the longitudinal cohorts. Each participant is given a unique identifier, and each visit is preprogrammed as a defined event in the CSpro data collection instrument to facilitate data entry. The surveys will be conducted by CHVs familiar with the participants and will be prompted to confirm the identity of the participants before data entry. In addition, the data manager will confirm the data quality on the server once a week. Access to survey data will be limited to data analysts and the data manager in the research team. In addition, personally identifiable information will be removed before data analyses.

### Confidentiality {27}

To maintain confidentiality, each participant in this study is assigned a unique identifier. The data collected will be labeled using the unique identifier and stored separately from the key linking personal information (name, date of birth, GPS, and phone number). The data will be kept on a secure server that is only accessible to research staff. Publications will contain only aggregated data, and no personal information will be included.

### Plans for collection, laboratory evaluation and storage of biological specimens for genetic or molecular analysis in this trial/future use {33}

Blood samples will be collected to examine malaria infections by multiple methods, immunity against malaria parasites and mosquito saliva, and malaria parasite genomics. No human genetic studies are planned in this study. However, any biological specimens remaining after analyses described in this study will be stored indefinitely for future studies unless the participants opt out during the informed consent process. Contact information of the study team is provided in the consent form to study participants, who can remove themselves from this study and any future studies that may use their blood samples at any time without penalty or prejudice.

## Statistical methods

### Statistical methods for primary and secondary outcomes {20a}

The intention-to-treat (ITT) analysis is the primary analysis approach for both the primary and secondary outcomes and the per-protocol analysis will be included as a supplementary analysis.

The primary outcome of the study is malaria prevalence by PCR of children aged 0 to 15 6 months after the financial incentive intervention. Based on the PCR examination results, we apply a regression model for two-stage randomized control trial settings, proposed by a study [11], which allows us to identify an unbiased estimate of the ITT and also the spillover effects on treated and untreated households within a cluster while controlling for confounders, including age, gender, house structure, and other socioeconomic status indicators.

For secondary outcomes, the PCR malaria prevalence of all the age groups, the microscopic malaria prevalence, the proportion of participants using the bed net, and the malaria knowledge of the adult participants will be evaluated similarly.

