**Fig. 1 Fig1:**
[figure not shown]
Map of Suba South showing the locations and the types of arms of the 92 trial clusters

The randomization at the second stage is done at the household level in the two intervention arms, CCT and LIS, to determine which households will receive the treatment within an intervention cluster. It is designed to measure spillover effects within an intervention cluster from the households with treatment to those without treatment. The random assignment at the household level within an intervention cluster is made by asking a household representative to draw a scratch card during a site visit by the survey team for the intervention. The card has a single number from 1 to 10 printed under a seal. If an even number appears on the card drawn, the household will receive the treatment, meaning that (1) the household receives the malaria education (EDU) at the site visit and (2) its household members become eligible for an incentive scheme (CCT or LIS depending on the arm of the cluster). The household will not receive the treatment otherwise.

A power analysis was conducted after taking into account the size of the expected intervention effect, the number of clusters, and the number of households and individuals following a recent examining regression models for a random saturation experiment [11], which fits our two-stage randomization setting. The two intervention arms, CCT and LIS, are randomly assigned to 32 clusters, respectively, while the control arm is assigned to 28 clusters. The cluster-level randomization is supplemented by intra-cluster random assignment at the household level, and the overall structure of the experiment forms a two-stage randomized control trial.

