## Appendix

### The English translation of the intervention script

The following script is used for all the target households:

*We would like to ask all of you who have been cooperating in this research project to continue to join it. As you all know, Homabay County has a very high rate of malaria prevalence. The most effective prevention method is the proper use of insecticide-treated mosquito nets. However, it is not being thoroughly implemented. If we implement appropriate preventive actions, including the use of mosquito nets, and early diagnosis and treatment in health facilities when the infection is suspected, we should be able to contain malaria transmission in the region.*

The following script is used for the households in treatment clusters (CCT and LIS):

*In order to encourage such appropriate preventive actions, this research project will experiment with an educational tool to increase knowledge about malaria and a reward scheme for your efforts to avoid contracting malaria. The reward scheme is to reward those who are confirmed to be malaria-negative at the next survey scheduled in 6 months when the RDT test is conducted. All persons listed under this household in this survey are eligible.*

*Please note that this is an experimental trial with a limited budget; not all households can be eligible for the reward this time. This time, 50% of the households who cooperate with the survey will be eligible for the reward scheme.*

*Whether or not a household is eligible for the reward system will be determined by a scratch card. We will ask a representative of the household to draw a card, and if a card with an even number is picked, the household will be eligible for the reward scheme.*

*If this experiment is successful, we will consider continuing the reward scheme and implementing policies to target more households.*

*If you agree, you will be asked to pick a scratch card. A scratch card has a number from 1 to 10 printed under the seal. You and your family members are eligible for the reward scheme if you draw a card with an even number, i.e., 2, 4, 6, 8, or 10.*

*Please choose who will draw a scratch card?*

[Enumerator Instruction] Ask a respondent to draw a card from the envelope with 10 cards. Once s/he draws a card, remove the seal by a coin in front of them and share the result with them.

The following script is used for the eligible households in CCT clusters:

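### With one assigned coverage level (50%) in every intervention cluster, the design does not identify spillover on treated households, although {20a} says the regression does

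*Protocol article*

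**What the plan says.** Section {20a} of the protocol article applies a regression for two-stage randomised trials, "which allows us to identify an unbiased estimate of the ITT and also the spillover effects on treated and untreated households within a cluster", with adjustment for age, gender, house structure and socioeconomic indicators. It names no further assumption.

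The second stage is the same in both intervention arms. Under Trial design {8}, "The card has a single number from 1 to 10 printed under a seal", and "If an even number appears on the card drawn, the household will receive the treatment". Intervention description {11a} has the household representative "draw a card from an envelope containing ten cards". Sample size {14} takes it that "ten households in a treatment cluster end up receiving the treatment, and the remaining ten households are left untreated". The Appendix script, common to CCT and LIS clusters, tells participants that "50% of the households who cooperate with the survey will be eligible for the reward scheme". No second coverage level appears anywhere.

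Trial design {8} gives the second stage a narrower purpose than {20a}: to measure spillover running from treated to untreated households within an intervention cluster. Section {14} powers both a direct and a spillover effect, each relative to control, and does not define *direct*.

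**The concern.** To estimate spillover on treated households, one must compare treated households that have different shares of treated neighbours. This design assigns treated households only one share. A figure reported as spillover on the treated, or as an own-treatment effect net of spillover, would look like a randomised result but would depend on an assumption the reader has not been shown.

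This matters because spillover is a secondary objective ({7}) and part of the Discussion's economic case for paying incentives. The results are also to go to county and national malaria programmes considering expansion ({31a}).

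**Working it through.** **The plan's own figures.** Even numbers among 1 to 10: 5/10 = 0.5. Treated households per intervention cluster: 0.5 × 20 = 10. Clusters: 28 + 32 + 32 = 92. Households: 92 × 20 = 1840. Individuals: 1840 × 5 = 9200. All agree with {14}.

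**Counting what is identified.** Each arm and the control give three cell means. Take four parameters: control level, own-treatment effect, spillover on untreated households, spillover on treated households.

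| Cell | Control level | Own | Spillover, untreated | Spillover, treated |
|---|---|---|---|---|
| Control, 0% | 1 | 0 | 0 | 0 |
| Untreated, 50% | 1 | 0 | 1 | 0 |
| Treated, 50% | 1 | 1 | 0 | 1 |

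The matrix has rank 3 for 4 parameters. The own and treated-spillover columns are identical, so only their sum can be estimated. A larger sample or more covariates cannot change that.

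**What the data could not distinguish.** Section {14} plans a fall from 30% to 21%, or 9 points. For treated households these splits give the same cell means:
- own −9, spillover 0
- own −4.5, spillover −4.5
- own 0, spillover −9

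**What would separate them.** If spillover is assumed equal on treated and untreated households, there are 3 parameters and rank 3, so the split is identified by assumption. With two interior coverage levels (0.3 and 0.7, for illustration only) and linear spillover, the rank is 4 of 4.

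**Chance variation in realised coverage.** If each household draws independently, the treated share among a household's 19 cluster neighbours has SD √(0.25/19) = 0.115. Assume a linear effect of that share in treated households, prevalence 21%, ICC 0.05 ({14}) and 32 clusters per arm. Let n be the number of analysed persons in treated households per cluster. Here n = 50 is 10 households × 5 persons, and n = 25 is an assumption for fewer analysed persons. Then

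SE(slope) = √(0.21 × 0.79 × [0.05 + 0.95/n]) / (0.115 × √32)

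- n = 50: √(0.1659 × 0.069) = 0.107; 0.107/0.649 = 0.165. Going from 0 to 50% coverage, the SE is 0.5 × 0.165 = 0.082. The minimum detectable effect at 80% power is 2.80 × 0.082 = 0.231.
- n = 25: √(0.1659 × 0.088) = 0.121; 0.121/0.649 = 0.186; SE 0.093; minimum detectable effect 0.261.

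That is 23 to 26 points, against a planned effect of 9 points and a baseline of 30%. If exactly ten households per cluster are treated, as {14} describes, this variation is zero and the approach is unavailable.

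**The case against.** The clause in {20a} could be loose wording for two effects per arm, one for treated and one for untreated households. Trial design {8} and Sample size {14} support that intention. The literal words, however, list the ITT and, in addition, spillover on both groups, so the sentence still needs correcting.

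The regression equation sits in a cited paper that is not at hand, and an equal-spillover or parametric assumption may appear in a fuller plan. That is fair, and its absence from an article is not the point. The point is that {20a} presents the quantity as identified without bias, and no later document can add a comparison group that the randomisation did not create.

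Local exposure also varies more than cluster-wide coverage. For the nearest five households (an illustrative number), independent draws give SD √(0.25/5) = 0.22. GPS coordinates are recorded, and the Discussion considers a method for interference between clusters. So some information about treated households does exist. It concerns a different, local quantity that {20a} does not specify, and it would need a model.

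Three stronger readings are tempting but not supported:
- That the primary analysis is undermined. It is not: treated households versus control, untreated households versus control, and all households versus control keep their randomised comparison.
- That *direct* in {14} is an error. The word is undefined there. Read as treated households relative to control, it is an identified effect that includes any spillover received.
- That the two parts can never be separated. They can be under a stated assumption, but not by the randomised design alone.

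**Conclusion.** The point holds as a correction to one stated claim. Spillover on treated households is not identified by randomisation: each arm gives two independent contrasts with control, while {20a} lists an ITT and two spillover effects. This follows from the assignment rule and does not depend on the ICC, the sample size or the cited method.

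The 23 to 26 points only indicates how little chance variation could offer. It rests on independent card draws, a linear effect, ICC 0.05 and the stated range of n. The article does not say whether the envelope is refilled between households. Pooling the two schemes would lower the figure, but {14} compares each arm with control separately.

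Reading the remaining contrasts as effects of 50% versus 0% coverage also assumes that control clusters receive no spillover from neighbouring intervention clusters. The Discussion already acknowledges that this may fail.

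**What to change.** In {20a}, name the contrasts that each arm identifies against control, each at 50% coverage: treated households (total effect, own plus any spillover received), untreated households, and all households in the cluster. The sponsor should say which of these is the primary ITT contrast, since {20a} does not.

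Delete spillover on treated households from the identified quantities. Alternatively, keep it as an exploratory estimate with its assumption written beside it: equal spillover on treated and untreated households, or a specified model in realised or local coverage. The same label should go on any treated-minus-untreated difference presented as an own-treatment effect.

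In {14}, add that *direct* relative to control means the total effect on treated households. If a precision figure is quoted, base it on 32 clusters per arm.

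Follow-up ended in February 2023, so coverage can no longer be varied. The cost is rewording, one decision by the sponsor on the primary contrast, and one claimed estimate withdrawn or relabelled.
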